### 3.9. Laboratory measurements

Blood and urinary levels of biomarkers of inflammation (IL-2, IL-6, IL-10, TNF-alpha, 8-iso^-^prostanglandin^-^F_2*α*_) and of endothelial function [Endocan, angiopoietin^-^1 (Ang^-^1), angiopoietin^-^2 (Ang^-^2), vascular endothelial (VE)^-^cadherin] will be measured from blood and urinary samples performed the day before surgery, on arrival in the ICU and at 24 hours and at 48 hours after admission in the ICU. Additional blood and/or urinary analysis will be performed if necessary, depending on the hypotheses formulated from the results of the study.

### 3.10. Safety

All serious adverse events will be collected and reviewed by the principal investigator and reported to the trial sponsor (CHU Besancon, Besancon, France). Study insurance has been contracted for all participants by the trial sponsor (CHU Besancon, Besancon, France).

The use of the MooKy HR memory® device and of the Abbott® FreeStyle Libre Pro subcutaneous glucose sensor comply with the CE marking and with the recommendation of the manufacturer.

### 3.11. Sample size calculation

Four groups of patients will be included to describe the relationship between preoperative (baseline) and early postoperative BG variability in diabetic (groups 1 and 2) and non^-^diabetic patients (groups 3 and 4), and between BG variability and the ANS activity in patients treated (groups 1, 2 and 4) or not (group 3) with beta^-^blockers: group 1, including patients with insulin^-^requiring type 2 diabetes mellitus undergoing planned on^-^pump CABG surgery; group 2, including patients with non^-^insulin^-^requiring type 2 diabetes mellitus undergoing planned on^-^pump CABG surgery: group 3, including non^-^diabetic patients undergoing planned aortic valve replacement surgery; and group 4, including non^-^diabetic patients undergoing planned on^-^pump CABG surgery.

No previous study has described the difference between the preoperative (baseline) and the early postoperative CV (primary outcome) in cardiac surgery patients. Thus, no assumption can be made on the expected value of the primary outcome. The sample size calculation was based in the expected measurement accuracy of the primary outcome in each group.

Considering an alpha risk at 0.05 and an estimated standard deviation of CV of 8.2 (basal state) (RE Pratley, 2018 Nov), we hypothesized that the 95% confidence interval range of the difference between the baseline and the early postoperative CV will be no more than 6.12 (conservative assumption considering that the variance will be lower because of the repeated measurement of CV in the same patients). A sample size of 30 patients per group was calculated using the PASS software (“Confidence Intervals for 1 Mean” method, Hahn, G.J. and Meeker, W.Q. 1991. Statistical intervals. John Wiley & Sons. New York).

Thus, the inclusion of a total sample size of 120 patients (30 patients per group) is planned.

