### 3.2. Eligibility

Adult patients who undergo planned on-pump coronary artery bypass surgery or aortic valve replacement surgery in the University Hospital of Besancon, France (Centre Hospitalier Universitaire (CHU) de Besancon) will be eligible for inclusion.

Four groups of 30 patients will be studied: group 1, including insulin-requiring type 2 diabetic patients undergoing on-pump coronary artery bypass graft (CABG); group 2, including non-insulin-requiring type 2 diabetic patients undergoing on-pump CABG; group 3, including non-diabetic patients undergoing aortic surgical valve replacement; and group 4, including non-diabetic patient undergoing on-pump CABG.

Inclusion and exclusion criteria for the present study are listed below.

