### 3.3. Inclusion criteria

Signed informed consent.Planned on-pump CABG or aortic valve replacement surgery (see above).Patient affiliated to French Social Security or equivalent.Ability to speak, write and understand French language.

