### 3.5. Study procedure and patient management

Eligible patients will be screened and informed during the anesthesia consultation. Written informed consent will be obtained the same day by investigators after an oral explanation of the study.

After inclusion in the study, patient characteristics, past medical history including ASA physical status and Euroscore value, and preoperative fasting BG and glycosylated hemoglobin values will be collected.

All patients will be admitted to the Cardiac Surgery Department the day before surgery. All patients included in the study will be managed according to the current practices for the management of patients undergoing planned cardiac surgery. Briefly, on arrival in the operating room, standard monitoring (Carescape B850 monitor, General Electric Healthcare, USA) will be set up. A dedicated peripheral venous catheter will be inserted in a forearm vein to infuse anesthetic drugs. All patients will receive manually driven target^-^controlled infusion of propofol and remifentanil to maintain bispectral index (BIS) values between 40 and 60. All patients will be paralyzed using non depolarizing neuromuscular blocking agent (either cisatracurium or atracurium). After induction of anesthesia, patients will be intubated, and tidal volume and respiratory rate will be set to maintain the end^-^tidal carbon dioxide between 35 and 40 mm Hg. Inspired oxygen fraction will be adjusted to obtain a pulse oximetry ≥ 95%. A central venous catheter inserted in the internal jugular vein, a urinary catheter and an indwelling arterial catheter introduced in a radial artery will be implemented. No intravenous glucose will be administered intraoperatively in the absence of hypoglycemia (defined as <75 mg/dL [4.1 mmol/L]). Tranexamic acid (1.5 g before incision and 1.0 g before surgical wound closure) and antibiotic prophylaxis with cefuroxime (1.50 g before skin incision, reinjection at priming of the extracorporeal circulation and then 0.75 g every 2 h until end of surgery) or linezolid 600 mg in case of allergy to cefuroxime will be initiated before incision.

Intraoperative data describing the surgical procedure and the anesthetic management will be obtained from the computerized anesthesia monitoring sheet: type and duration of surgery; duration of aortic cross clamping; duration of extracorporeal circulation; intraoperative blood loss and urine output; intraoperative blood transfusion and total volume of fluids infused.

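### Section 3.11 reads beta-blocker treatment off the surgical group, and its diabetic/non-diabetic grouping mixes in valve surgery, so neither split isolates the factor it names

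*Protocol article*

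**What the plan says.** Section 3.11 of the protocol article explains the four groups by two groupings. The first concerns baseline and "early postoperative BG variability in diabetic (groups 1 and 2) and" non-diabetic patients, the latter being groups 3 and 4. The second concerns the relation between glucose variability and "the ANS activity in patients treated (groups 1, 2 and 4) or not (group 3) with" beta-blockers.

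Section 3.2 defines the groups by diabetes or insulin status and by operation only: "group 3, including non-diabetic patients undergoing aortic surgical valve replacement", and "group 4, including non-diabetic patient undergoing on-pump CABG". Groups 1 and 2 are also on-pump CABG. The surgical inclusion criterion in section 3.3 is "Planned on-pump CABG or aortic valve replacement surgery (see above"). Nothing in sections 3.2 to 3.4 requires beta-blockers in groups 1, 2 and 4 or excludes them in group 3.

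The baseline data in section 3.5 cover "patient characteristics, past medical history including ASA physical status and Euroscore value", with fasting glucose and glycosylated hemoglobin. Beta-blocker use is not named. Section 2 lists diabetic status and type of surgery as two factors. Section 3.12 gives unadjusted group tests, correlation coefficients and univariate linear regression, and states no covariate or stratification.

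**The concern.** The beta-blocker clause turns an expectation about usual treatment into a label for each patient. A valve patient who takes a beta-blocker would be described as untreated, and a CABG patient who does not would be described as treated. Even if the label were correct for everyone, it would coincide with type of surgery. Differences in autonomic activity, or in its relation to glucose variability, could then come from the operation, the underlying heart disease, diabetes or beta-blockade, with no means of telling which.

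The diabetes grouping has a milder form of the same fault. All diabetic patients have CABG, while half of the pooled non-diabetic patients have valve surgery. A difference read as a diabetes effect would be partly a surgery effect, although section 2 treats the two factors as separate.

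At stake is the interpretation of the secondary descriptions by diabetic status and of those involving autonomic activity.

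**Working it through.** **Inputs.** Group definitions come from section 3.2. The groupings, SD 8.2, interval width 6.12 and n = 30 per group come from section 3.11. CABG-valve differences and beta-blocker rates are not in the document, so any used below are assumptions.

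**The plan's own figure.** The full width of a 95% interval for one mean is 2 × t(0.975, n−1) × SD/√n. At n = 30 this is 2 × 2.045 × 8.2/√30 = 6.124, which matches 6.12 to rounding. The sample size is reproduced and is not in question.

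**Composition of the two groupings.**

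| Grouping | Side | Patients | CABG | Valve | Diabetic |
|---|---|---|---|---|---|
| Diabetes | Groups 1+2 | 60 | 60 | 0 | 60 |
| Diabetes | Groups 3+4 | 60 | 30 | 30 | 0 |
| Beta-blocker | Groups 1+2+4 | 90 | 90 | 0 | 60 |
| Beta-blocker | Group 3 | 30 | 0 | 30 | 0 |

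**What a difference in means would contain.** Let D be the diabetes effect, S the CABG-minus-valve difference and B the beta-blocker effect, taken as additive. Let p(CABG) and p(valve) be the proportions actually treated.

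- Diabetes grouping, leaving B aside: D + S × (60/60 − 30/60) = D + S/2.
- Beta-blocker grouping: B × [p(CABG) − p(valve)] + S × (1 − 0) + D × (60/90 − 0/30) = B × [p(CABG) − p(valve)] + S + (2/3)D.

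The S/2, S and (2/3)D terms follow from the group sizes and additivity alone. The multiplier on B does not. If 70% to 100% of CABG and 0% to 40% of valve patients were treated (assumed), it would lie between 0.70 − 0.40 = 0.30 and 1.00 − 0.00 = 1.00.

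**Illustration for the diabetes grouping.** Suppose D = 0, SD = 8.2 and a two-sided 5% comparison of means. The standard error is 8.2 × √(1/60 + 1/60) = 1.50.

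| Assumed S (CV points) | Spurious difference S/2 | Rejection rate |
|---|---|---|
| 2 | 1 | about 10% |
| 4 | 2 | about 27% |
| 8 | 4 | about 76% |

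These use a normal approximation with the SD held at 8.2. Mixing two operations widens the spread in the non-diabetic set, so an actual t test would reject somewhat less often.

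**Cost of the cleaner contrasts.** At SD 8.2:

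- Diabetes within CABG, 60 versus 30: SE = 8.2 × √(1/60 + 1/30) = 1.83. The ratio to the pooled SE is 1.83/1.50 = 1.22. The 95% interval width is 7.29, against 5.93 for 60 versus 60.
- Surgery within non-diabetics, 30 versus 30: the interval width is 8.48.

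**The case against.** The strongest reply is that section 3.11 fixes no contrast. It speaks of describing relationships in each kind of patient, which can be read as within-stratum description. It assigns no test or model to the pooled groups. Section 2 keeps diabetic status and type of surgery apart, precision is set in each group, and group 4 already allows 1+2 versus 4 and 3 versus 4. The choice of contrast may be made in a full protocol or analysis plan that is not shown. Beta-blockers appear nowhere in the objectives, outcomes or analysis section.

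Much of this stands, and it rules out several stronger readings:

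- A reader might infer that a formal test of groups 1+2 against 3+4, or an estimate of a beta-blocker effect, is planned. The document states neither.
- A reader might infer that beta-blocker use will not be recorded. The list in section 3.5 is introduced as non-exhaustive and this is a condensed article, so one can say only that the item is not named.
- A reader might take the rejection rates as properties of this study. They rest on assumed surgery effects and concern means. No bias in a correlation or slope was computed, and 8.2 is a baseline SD.

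What the reply does not remove is the text itself. Section 3.11 says which groups are treated and which are not, and no criterion makes that true. A description under a wrong label is still wrong, and a reader who sets the two strata side by side is comparing operations. The diabetes grouping is likewise stated in 3.11, and nothing in 3.12 separates surgery from it.

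**Conclusion.** The point holds for the two groupings as stated. The beta-blocker split is identical to type of surgery and differs by 67 percentage points in diabetes (60/90 versus 0/30), so differences across it cannot be attributed to beta-blockade. The diabetes grouping carries half of any CABG-valve difference in a comparison of means. Both statements follow from the group definitions, under additive effects. How large the distortion would be is unknown, because the document gives neither a surgery effect nor treatment rates.

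The consequence is confined to secondary objectives. It would go too far to infer that the primary result or the sample size is compromised: the primary outcome is a within-patient change in CV, and the 6.12 width and 30 patients are set for each group separately. The four-group design is also sound, since it already contains the cleaner contrasts.

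**What to change.** 1. In section 3.11, stop presenting groups 1, 2 and 4 as treated and group 3 as untreated. Classify exposure by each patient's recorded beta-blocker treatment, before surgery and over the 48 postoperative hours. Use that variable in the autonomic analyses, adjusted for group or type of surgery. Confirm that the data collection captures it; if not, it is one item from the medical record.
2. Describe diabetic status within CABG (groups 1+2 versus 4) and type of surgery within non-diabetics (group 3 versus 4). Alternatively, fit one model to all 120 patients with separate diabetes and surgery terms. Because no diabetic patient has valve surgery, that model estimates the diabetes effect from the same CABG patients.
3. State in section 3.12 that comparisons by diabetic status, surgery or beta-blockade use these definitions.

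The cost is wording and possibly one data item, with no added patients or visits. The price in precision is a standard error about 22% larger for the diabetes contrast (1.83 versus 1.50 at SD 8.2). One limit remains: adjusted for surgery, a beta-blocker effect can be estimated only from patients within an operation who differ in treatment. If almost none do, the report should say that the two cannot be separated.

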## 1. Introduction

Blood glucose (BG) variability in diabetic and non-diabetic patients is independently associated with increased morbidity and mortality in the intensive care unit and after cardiac events.^[1–3]^ In cardiac surgery patients, BG variability is reported to be associated with severe postoperative complications – leading to an increase length of intensive care unit (ICU) stay – regardless of the quality of BG control obtained during the perioperative period.^[4–6]^

Several hypotheses have been raised to explain the deleterious effect of BG variability observed in diabetic patients. Basal state BG variability seems to depend on the diabetes phenotype and to differ between people with or without diabetes.^[7,8]^ Furthermore, some studies suggest an association between BG variability and the activity of the autonomic nervous system (ANS).^[9–13]^ Finally, other studies highlight that the deleterious effect of BG variability includes increased oxidative stress, endothelial dysfunction, and cell apoptosis.^[14–16]^ However, no study has specifically addressed this issue in cardiac surgery patients and the underlying mechanisms contributing to increased perioperative BG variability and to its deleterious impact remain unclear.

The aim of this study is to investigate whether postoperative GV could be related to preoperative GV and/or to perioperative alteration of the ANS activity in diabetic and non-diabetic cardiac surgery patients and the relationship between postoperative GV and blood and urinary level of inflammation and endothelial dysfunction biomarkers.

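### The planned 95% CI width of 6.12 uses the SD of a single CV as the SD of the paired difference, and repeated measurement does not make that conservative

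*Protocol article*

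**What the plan says.** Section 3.8 defines the primary outcome as the mean difference between preoperative and postoperative CV, with its 95% confidence interval. Section 3.11 says that no earlier study has described this difference, so the sample size rests on the expected accuracy of the estimate in each group.

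The inputs in section 3.11 are an alpha of 0.05 and an SD of CV of 8.2, labelled as a basal-state value. The authors hypothesise that "the 95% confidence interval range of the difference between the baseline and the early postoperative CV will be no more than 6.12". The parenthesis that follows calls this a "conservative assumption considering that the variance will be lower because of the repeated measurement of CV in the same patients". The method is the PASS procedure "Confidence Intervals for 1 Mean", and the result is 30 patients per group, 120 in all.

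No correlation between the two CV values, no SD of the postoperative CV and no SD of the difference is given anywhere in the article.

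**The concern.** The interval is for a mean of within-patient differences, so the SD it needs is that of the difference. The only SD supplied is that of one measurement at one time. Replacing one with the other can err in either direction, depending on the correlation between the two measurements and on how their spreads compare.

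The article says the substitution errs on the safe side because the same patients are measured twice. Pairing does lower the variance of a difference, but relative to two independent samples (2 × SD²). It need not bring it below the variance of one measurement (SD²), which is what the calculation used.

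This figure is the only quantitative basis for 30 per group. A reader is told that the precision in each group will be at least this good, and nothing in the article supports that direction.

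**Working it through.** **Inputs.** From section 3.11: SD of a single basal CV = 8.2, 95% two-sided interval, n = 30 per group, one-mean method, stated width 6.12. The correlation ρ and the post/pre SD ratio k are not in the article; they are assumptions, shown as ranges.

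**Step 1: reproduce the stated figure.** Width = 2 × t(0.975, n − 1) × SD / √n.

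2 × 2.045 × 8.2 / √30 = 6.124, stated as 6.12. Solving for n gives 30 at a width of 6.125 and 31 at a strict 6.12, which is rounding only. The normal-quantile version gives a width of 5.87, and reading 6.12 as a half-width would need only 10 patients. So 6.12 is the full width of a t interval with SD 8.2, and 8.2 was entered as the SD of the difference.

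**Step 2: SD of the paired difference.** In general, SD_diff = √(SD₁² + SD₂² − 2ρ·SD₁·SD₂). With both SDs equal to 8.2, this is SD_diff = 8.2 × √(2(1 − ρ)). It is at or below 8.2 exactly when 2(1− ρ) ≤ 1, that is, when ρ ≥ 0.5.

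**Step 3: width with 30 per group, SD 8.2 at both times.**

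| ρ (assumed) | SD_diff | 95% CI width | n per group for width 6.12 |
|---|---|---|---|
| 0 | 11.60 | 8.66 | 58 |
| 0.3 | 9.70 | 7.25 | 42 |
| 0.4 | 8.98 | 6.71 | 36 |
| 0.5 | 8.20 | 6.12 | 31 (30 with the article's rounding) |
| 0.7 | 6.35 | 4.74 | 20 |

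Relative to 6.12, the interval is 18% wider at ρ = 0.3 (7.25/6.12 = 1.18) and 41% wider at ρ = 0 (8.66/6.12 = 1.41).

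**Step 4: unequal SDs.** Put SD₂ = k × 8.2. Then SD_diff ≤ 8.2 when k² − 2ρk ≤ 0, that is, when ρ ≥ k/2. With n = 30:

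| k (assumed) | Break-even ρ | Width at ρ = 0.3 | Width at ρ = 0.5 |
|---|---|---|---|
| 0.75 | 0.375 | 6.46 | 5.52 |
| 1 | 0.5 | 7.25 | 6.12 |
| 1.25 | 0.625 | 8.24 | 7.02 |
| 1.5 | 0.75 | 9.39 | 8.10 |

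The threshold of 0.5 therefore belongs to the equal-SD case and shifts in either direction with k.

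**The case against.** The strongest defence is that little depends on 6.12. The study is observational and descriptive, and no power, type I error or decision rule uses the figure. The published interval will be computed from the observed differences. The authors say openly that no prior data exist, so any SD of the difference would have had to be assumed. Under the constant glucose infusion and protocolised insulin of section 3.5, the spread of postoperative CV could be smaller than at baseline, and 6.12 might then be met at a correlation below 0.5. All of this stands and limits the severity. It does not rescue the stated reason: making an assumption was unavoidable, but calling it conservative because of pairing is wrong.

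A reader might infer more than the article supports:

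- **That 6.12 is offered as a guarantee.** Even with a true SD of 8.2 for the difference, the observed width would exceed 6.12 about half the time. But that is true of nearly any expected-width calculation, and section 3.11 speaks of a hypothesis and of expected accuracy.
- **That one SD for four groups understates the width.** The Introduction says "Basal state BG variability seems to depend on the diabetes phenotype and to differ between people with or without diabetes". It does not say that the between-patient SD of CV exceeds 8.2 in any group; in some groups it may be lower.
- **That sensor loss will shrink the groups.** Section 3.6 mentions accidental removal in order to arrange recovery of the stored readings. Attrition detail may also sit in the full protocol.
- **That the study is too small.** The last column of the Step 3 table only converts the stated width into patients. The article gives no reason why 6.12 in particular is needed, and an interval pooled over all 120 patients would be narrower.

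**Conclusion.** The point holds as a misstatement of planning precision, of moderate severity. The arithmetic behind 30 per group is correct for the SD entered. The faults are that the SD belongs to a single measurement and that the reason for calling it conservative is invalid.

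If both SDs are 8.2, the stated width is reached only at a correlation of 0.5 or more; at lower correlations it is missed by up to about 41% (at zero correlation, and taking negative correlations as out of scope). The direction of the real error is unknown. The true correlation may exceed 0.5 or the postoperative spread may be smaller, and then 6.12 would be met or bettered. The documents do not show that the precision will be worse than stated, only that the claim of a safe margin has no support. Estimates and reported intervals are not biased by it.

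**What to change.** Keep 30 patients per group. In section 3.11, delete the parenthesis "conservative assumption considering that the variance will be lower because of the repeated measurement of CV in the same patients" and replace the single-width statement with wording such as:

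> With 30 patients per group and an assumed SD of CV of 8.2 at both times, the expected 95% CI width of the mean CV difference in each group is 4.7 points if the pre-post correlation is 0.7, 6.1 if 0.5, 7.2 if 0.3 and 8.7 if 0. The correlations are assumptions. A larger postoperative SD widens these intervals, and a moderately smaller one narrows them.

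The cost is a rewording of one section, with no extra patients and no change to the design or analysis. The stated precision becomes a range, part of which is less favourable than 6.12.

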### 3.4. Exclusion *criteria*

Emergent surgery defined by a surgery performed < 48 hours after the anesthesia consultation.Combined surgery (coronary artery bypass combined with valve surgery, multiple valve replacement, ascending aorta surgery).Off-pump CABG.Type 1 diabetes mellitus.Chronic preoperative heart rhythm disorder (regular extrasystoles, chronic atrial fibrillation).Pacemaker dependence.Body mass index < 18 kg m^–2^ or >35 kg m^–2^.Age under 18 years or over 80 years.Pregnant or breast^-^feeding women.Expected life expectancy < 48 hours.Legal incapacity or limited legal capacity.Subjects without health insurance.Subjects within the exclusion period of another study.

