### 3.6. Assessment of perioperative blood glucose variability

After written informed consent is obtained, a subcutaneous glucose sensor Abbott® FreeStyle Libre Pro will be applied in the fatty part of the back of the upper arm of included patients, as recommended by the manufacturer. The Abbot® FreeStyle Libre Pro glucose sensor will allow to measure the baseline BG variability during at least 2 consecutive days prior to surgery using the following parameters: the standard deviation (SD) of BG, the coefficient of glycemic variability (CV) (defined as the ratio of the SD on the mean BG expressed as a percentage), the mean of the daily differences between the higher and the lower values of BG (MAGE), the glycemic lability index and the glycemic penalty index. In case of accidental removal of the sensor during this period or delayed surgery > 14 days after the inclusion, patients will be informed to bring back the sensor the day before surgery so that all blood glucose measurements stored in the sensor can be collected.

The subcutaneous glucose sensor Abbott® FreeStyle Libre Pro will be changed the day before surgery and applied in the same area to measure postoperative BG variability up to 7 days after surgery using the same parameters as preoperatively.

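### The 30 patients per group calculated for a 95% CI width of 6.12 are also the 30 to be included, so at the stated SD the width has no margin for a patient without a paired CV

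*Protocol article*

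**What the plan says.** Section 3.8 of the protocol article makes the primary outcome the mean change in CV from before to after surgery, with its 95% confidence interval. Each patient therefore has to supply two sensor-based CVs.

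Section 3.11 sets precision separately in each group. It takes an SD of 8.2 for a basal-state CV and supposes that "the 95% confidence interval range of the difference between the baseline and the early postoperative CV will be no more than 6.12". It describes this as a "conservative assumption considering that the variance will be lower because of the repeated measurement of CV in the same patients". A one-mean confidence interval method then gives 30 per group, and the section closes: "Thus, the inclusion of a total sample size of 120 patients (30 patients per group) is planned".

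On timing, section 3.5 places consent at the anesthesia consultation: "Written informed consent will be obtained the same day by investigators after an oral explanation of the study". Under section 3.6 the first sensor goes on after consent and must record two or more days in a row before the operation. A second sensor is fitted the day before surgery. The same section foresees trouble with the first one: "In case of accidental removal of the sensor during this period or delayed surgery > 14 days after the inclusion". In those cases the patient returns the sensor so that its stored readings can be retrieved.

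Section 3.4 lists, among the exclusions, off-pump and combined surgery and "Emergent surgery defined by a surgery performed < 48 hours after the anesthesia consultation".

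**The concern.** The formula in section 3.11 returns the number of differences that must be analysed. The plan uses the same number as its count of inclusions. Between inclusion and a usable difference a patient can drop out of the primary outcome in several ways:

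- a baseline recording shorter than two days;
- a baseline sensor that is never returned;
- failure of the postoperative sensor within the 48 hours named in section 2;
- withdrawal;
- an operation that turns out to be of an excluded type.

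A patient with only one CV adds nothing to a paired difference. What is at stake is whether the width of 6.12, the only precision figure that the article gives for the primary outcome, is what 120 inclusions can be expected to deliver in each group.

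**Working it through.** **Inputs from section 3.11:** two-sided 95% confidence, SD = 8.2, full width 6.12, 30 per group. The document gives no loss rate and no pre/post correlation, so both are varied below as assumptions.

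**Step 1: reproduce the plan's figure.** For a one-mean t interval,

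width = 2 × t(0.975, n − 1) × SD / √n.

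With n = 30: 2 × 2.045 × 8.2 / √30 = 6.124, which rounds to the stated 6.12. The normal approximation would need only 28 patients, and reading 6.12 as a half-width would need only 10. The plan's figure is therefore the t-based full width, met at exactly 30 analysed differences.

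**Step 2: same SD, fewer complete pairs.**

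| Complete pairs of 30 | Loss | Width | Relative to 6.124 |
|---|---|---|---|
| 30 | 0 | 6.12 | reference |
| 29 | 1 patient | 6.24 | +2% |
| 27 | 10% | 6.49 | +6% |
| 24 | 20% | 6.93 | +13% |

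**Step 3: does pairing supply the margin?** The 8.2 is the SD of a single CV, used as the SD of a difference. If the pre- and postoperative SDs are equal and their correlation is ρ,

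SD of the difference = 8.2 × √(2(1 − ρ)).

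This equals 8.2 at ρ = 0.5, is smaller above that value and larger below it.

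| ρ (assumed) | SD of difference | Width with 30 pairs | Pairs needed for 6.12 |
|---|---|---|---|
| 0 | 11.60 | 8.66 | 58 |
| 0.25 | 10.04 | 7.50 | 44 |
| 0.4 | 8.98 | 6.71 | 36 |
| 0.5 | 8.20 | 6.12 | 30 |
| 0.6 | 7.33 | 5.48 | 25 |

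Turning the formula round, the largest SD that keeps the width at 6.12 is 6.12 × √n / (2t). For 27 pairs this is 7.74, so ρ must be at least 1 − (7.74/8.2)²/2, about 0.56. For 24 pairs it is 7.25, so ρ must be at least about 0.61.

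**Step 4: how firm is 6.12 even with no losses?** With 30 pairs, a true SD of 8.2 and normal data, the observed variance follows a scaled chi-square distribution on 29 degrees of freedom. The realised width then has a 95% range of about 4.6 to 7.7 and exceeds 6.12 about 47% of the time.

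**The case against.** The strongest reply is that little depends on the number. The study is descriptive, with no power claim, margin or decision threshold tied to 6.12, and step 4 shows that chance alone moves the realised width further than a 10% loss would. That stands, and it is why the point is minor.

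The second reply is that the plan claims slack through pairing. That is possible, and at ρ = 0.6 it would cover the loss of five patients. But the slack needs ρ above 0.5 and the article gives no basis for such a value, so the claim is neither shown nor refuted.

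A reader might also infer more than the article supports:

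- **That lost patients will not be replaced.** The article does not address replacement. The full protocol, which is not shown, may do so.
- **That a dislodged sensor or postponed operation costs the pair.** Section 3.6 retrieves the stored baseline readings in both cases. A postoperative sensor that fails after 48 hours need not cost the pair either, on the window given in section 2.
- **That losses will differ between groups.** Nothing in the document bears on this.
- **That surgery within 48 hours of the consultation can be recognised only after inclusion.** Entry requires planned surgery, and its date may already be known at the consultation.

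The moment of inclusion is itself not clean. Sections 3.5 and 3.6 put consent and the first sensor at the consultation, whereas section 4.1 speaks of consent before inclusion on the eve of surgery. The latter does not fit a baseline of two or more days, and the passages should be reconciled.

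**Conclusion.** The point holds in a limited form. On the article's own inputs, the calculated number and the number of inclusions are the same, no allowance is stated for patients without both CVs, and the width of 6.12 corresponds to 30 complete pairs. The pairing argument does not fill the gap without a correlation above 0.5 under equal SDs.

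It would go too far to say that the precision fails in any group that loses a patient. The figure is a planning width at an assumed SD, not a guaranteed result. The expected effect is an interval about 6% wider at an assumed 10% loss and 13% wider at 20%, with SD 8.2 taken as stated. That is a modest change in a descriptive interval, so this is a minor correction to a stated design figure.

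**What to change.** In section 3.11, keep the 120 inclusions and add one sentence. It should say that the calculation refers to patients with an evaluable pre- and postoperative CV, and give the expected width per group over an assumed range of losses: about 6.5 at 10% and 6.9 at 20%, against 6.1 with none. The loss rates should be labelled as assumptions. If the pairing argument is kept, state the correlation that it relies on. In the results, report for each group the number of missing pairs and the reason for each.

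The cost is a sentence or two and a slightly less favourable stated figure. Including patients until 30 pairs are evaluable would also work (34 per group at an assumed 10% loss, since 30/0.9 = 33.3), but it enrols more patients and is not needed to correct the statement.
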